**Handling of missing data**

Detailed description of the patterns of missing data will be provided. This will include the proportion of missingness for each analysis model covariate and those used in the construction of the minimization criteria. We will not impute missing exposure or outcome data. Mothers with missing exposure data (i.e., no record of prescription of either labetalol or nifedipine) will be excluded from analysis. The magnitude and characteristics of these mothers will be summarized in a supplementary table.

**Handling of missing data using multiple imputation**

Multiple imputation will be performed using fully conditional specification (FCS) and the imputed datasets will then be used for the outcome analysis. Covariates that will be included in the imputation model are: all outcome covariates, exposure, the Giant PANDA minimization variables (excluding obstetric unit identifier and self-reported Black ethnicity), all covariates included in the selection and outcome models irrespective of missingness, and exposure and auxiliary covariates associated with the outcome.

It is important that the models used in the imputation phase are compatible with those used for the ATE estimation. This requirement means that choice of imputation model requires knowledge of the analysis model and the covariates used in both selection and/or outcome models. This ensures that there is compatibility between the two. This is an open area of active research, with methods chosen based upon current recommendations in the literature. Given our dataset is likely to have >50% missingness for some variables, it may not be possible to include these covariates in the model. These issues will be formally noted, along with the details of the explicit modelling choices made, and appropriate sensitivity analyses will be undertaken. When an interaction is possible between exposure and outcome model covariates, these will be included in the imputation model.

Standard imputation diagnostics will then be performed to assess the quality of the imputed datasets.

**Parametric and non-parametric causal models:** Potential estimators using multiple imputation (MI) datasets are (A) selection model, using inverse probability weighting (IPW); (B) outcome model, using regression adjustment (RA); (C) doubly robust augmented inverse probability weighting regression adjustment model (IPWRA); and (D) doubly robust targeted maximum likelihood estimation (TMLE) using machine learning algorithms.

**(A) Selection model using inverse probability weights (IPW)**

We will model exposure assignment using inverse probability weighted propensity scores, derived from the logistic exposure model, and including the minimization variables. Adequacy of balance achieved by propensity score weighting will be assessed using: (i) standardized mean difference for model covariates and variance estimates between exposure groups; and (ii) propensity scores overlap, to assess positivity assumption. A finding of lack of positivity will lead to measures such as: addition of interaction terms; different exposure models; use of alternate weighting structures (overlap or stabilized); and lastly, propensity score-based trimming, with the aim of achieving overlap in the propensity score distributions.

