**ANTICIPATED SAMPLE SIZE**

Our sample will comprise all women with hypertensive disorders of pregnancy (chronic hypertension, gestational hypertension, or preeclampsia) who birthed in Victoria between 2009 – 2020, and were prescribed either labetalol or nifedipine between 11-36 weeks’ gestation. In a blinded review of our data, we have determined our sample size to be approximately 7,500. Of these, approximately 90% received labetalol, and the remaining 10% received nifedipine. Based on this, we are powered to detect an exact difference between groups of ≥3.0% for the maternal primary outcome and ≥5.6% for the neonatal primary outcome.

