| **(F) Causal contrasts of interest** | **Binary Outcomes**  Relative risk (RR) and risk difference (RD) of each outcome (point estimate RR 95% CI) | **Causal comparison:**  *What is the causal effect of exposure to nifedipine during pregnancy on adverse maternal and perinatal outcomes, compared with exposure to labetalol?*  **Estimand = Average treatment effect (ATE)**  Relative risk (RR) and risk difference (RD) of developing each adverse outcome (ATE RR 95% CI).  ***Estimator model*** *–*Doubly robust inverse probability weighting with regression adjustment. |

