**Causal contrasts of interest**

1. **Estimand**

**Maternal outcomes** – relative risk (RR) and risk difference (RD) of primary composite outcome and pre-specified (*) secondary outcomes (ATE RR, 95% CI).

**Neonatal outcomes** – relative risk (RR) and risk difference (RD) of primary composite outcome and pre-specified (*) secondary outcomes (ATE RR, 95% CI).

In the Giant PANDA RCT, the primary neonatal binary outcome is estimated using a type of logistic regression (log-binomial) model. We will use a logistic regression model with robust standard errors (to adjust for maternal clustering). This model provides predictive probabilities that are then used to calculate both the between exposure difference (RD) and relative risk (RR) for all binary and highlighted (*) secondary outcomes.

In our emulated target trial, the estimand is the average treatment effect (ATE) between exposures, presented using both RD and RR metrics. Within the potential outcomes framework, a causal interpretation can be made under the assumptions of counterfactual consistency, ignorability (conditional exchangeability), and positivity. Counterfactual consistency means that the definition of exposure is consistent for all individuals. Ignorability states that treatment assignment can be considered exchangeable (i.e. as if the assignment was randomized) after controlling for, or conditioning on, a set of covariates. This implies that there are no important unmeasured confounders, an untestable assertion. The positivity assumption means that, for all observations, the conditional probability of being exposed and of not being exposed (receiving treatment or not receiving treatment) are both greater than zero.

1. **Estimators**

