In the emulated target trial, all estimators are targeting the ATE estimand detailed above. Each estimator is specific to the complete process used from the input (observational dataset) to model-based calculation of the ATE. These include: the methods and detailed modelling used in handling missing data; the analysis model used for outcome estimation; compatibility between the imputation and outcome models; and methods used to estimate variance when combining results across imputations and/or bootstrap samples. In the setting of complete data (following multiple imputation) both parametric doubly robust (DR) or non-parametric DR (e.g., machine learning data adaptive) methods, that combine selection and outcome regression models, can provide minimally biased ATE estimates if one of these regression models is correct. Valid 95% confidence limits require that uncertainties in both imputation and outcome models are accounted for (*vide infra*).

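### Overlap weights and propensity trimming are allowed if positivity fails, but a result from either would carry the ATE label while estimating the effect in a different population

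*SAP*

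**What the plan says.** The estimand is fixed in three places in the SAP. Row (F) of the Target Trial Emulation table names the ATE, with this estimator: "Doubly robust inverse probability weighting with regression adjustment". Under Causal contrasts of interest, "the estimand is the average treatment effect (ATE) between exposures, presented using both RD and RR metrics". The Estimators text that follows says: "In the emulated target trial, all estimators are targeting the ATE estimand detailed above".

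Section (A), on the selection model, covers what happens if propensity score overlap is poor. "A finding of lack of positivity will lead to measures such as" introduces a list: added interaction terms, different exposure models, then "use of alternate weighting structures (overlap or stabilized); and lastly, propensity score-based trimming".

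The SAP does not say that any of these measures changes the population to which the estimate refers. It does not rename the estimand when one is used or confine the measures to sensitivity analyses. It gives no threshold for the trigger and no trimming cut-off.

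**The concern.** A target trial emulation rests on a stated population and a stated contrast. Two of the listed measures change the population. Followed as written, the plan would still call the result the ATE, because the Estimators text makes no exception.

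This reaches the main analysis. Section (C) builds the doubly robust estimator from the selection model of section (A), so a change of weights or a trimmed sample there carries through to it. A reader would then compare a number for one group of women with estimates, and with a target trial, that refer to another, and nothing in the report would say so.

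**Working it through.** **Which population each method targets.** Let e(x) be the probability of nifedipine given covariates and τ(x) the effect at x. Weights h(x)/e(x) for nifedipine users and h(x)/(1−e(x)) for labetalol users estimate the average of τ(x) over the population with density proportional to h(x)f(x).

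| Method | h(x) | Target |
| --- | --- | --- |
| IPW | 1 | ATE |
| Stabilized IPW, normalised within arm | 1 | ATE |
| Overlap weights | e(x)(1−e(x)) | Overlap population (ATO) |
| Trimming | 1 inside the cut-offs, 0 outside | ATE in the women retained |

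The last two equal the ATE in general only if the effect, on the scale reported, does not vary across women.

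**How far the population could move: ART as an example.**

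Inputs: ART 8.7% (observed proportion, Details of imputation models); raw standardised difference 0.1759 (maternal balance table, Details of primary analysis models); 10% nifedipine and 90% labetalol (Anticipated sample size). The table does not state the direction of the difference, so both signs are shown.

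Solve (p1 − p0)/√{[p1(1−p1) + p0(1−p0)]/2} = ±0.1759 with 0.1·p1 + 0.9·p0 = 0.087.

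- *Nifedipine minus labetalol:* p1 = 0.136, p0 = 0.082. Then e(ART) = 0.1 × 0.136/0.087 = 0.156 and e(no ART) = 0.1 × 0.864/0.913 = 0.095. Overlap masses are 0.087 × 0.156 × 0.844 = 0.0115 and 0.913 × 0.095 × 0.905 = 0.078. The ART share becomes about 0.128, so about 9% moves to about 13%.
- *Opposite sign:* p1 = 0.047, p0 = 0.091, e(ART) = 0.054, e(no ART) = 0.104. The ART share becomes about 0.049, so about 9% moves to about 5%.

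**What that does to the estimate.** On ART alone and with the first sign, the share moves by 0.128 − 0.087 = 0.041. If the risk difference (RD) differed by 10 percentage points between ART and non-ART women (an assumption), the RD would move by 0.041 × 10 = 0.41 points. The SAP's stated detectable differences are 3.0% and 5.6%.

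**Larger shifts under assumed inputs.** Only the 10% exposure comes from the SAP.

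- *Two equal strata, RD −1% and +3%, so ATE = 1.00%.* With nifedipine probabilities of 5% and 15%, the overlap-weighted RD is (0.0475 × (−1) + 0.1275 × 3)/0.175 = 1.91%. With 2% and 18% it is 2.53%. If the RD is 1% in both strata, both methods give 1.00%.
- *Simulation of 2,000,000 records, 5% baseline risk, one confounder that also modifies the effect, true RD 0.60%:*

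| RD (share of records kept) | Weak selection | Moderate | Strong |
| --- | --- | --- | --- |
| IPW | 0.60% | 0.61% | 0.59% |
| Stabilized IPW | 0.60% | 0.61% | 0.59% |
| Overlap weights | 0.88% | 1.33% | 1.90% |
| Trim to 0.05–0.95 | 0.60% (100%) | 0.80% (90%) | 1.39% (65%) |
| Trim to 0.10–0.90 | 2.01% (47%) | 2.23% (42%) | 2.55% (36%) |

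With no effect in anyone, all methods agree at an RD of about 0. With about 10% exposed, many propensity scores lie near 0.10, which is why the choice of cut-off decides how many women are left.

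**Were overlap weights used for the primaries?** Overlap weights from a logistic propensity model balance the mean of every modelled covariate exactly; a numerical check gave differences of about 10⁻¹⁶. The weighted differences in the maternal balance table are not zero: body mass index 0.0193, SEIFA quintile 3 −0.0143, smoking 0.0124, all on the SAP's covariate list. The neonatal table likewise shows 0.0155, −0.0136 and 0.0132. This fits inverse probability weights and not overlap weights. It says nothing about trimming.

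**The case against.** The strongest reply is that the defect is largely hypothetical. The list is conditional and ordered: interaction terms and other exposure models come first and keep the ATE, and trimming comes last. Raw standardised differences are below 0.19, so selection on measured covariates looks modest, and the SAP reports good weighted balance for both primaries. This stands, with two limits. Balance is not positivity, and the overlap plots are not available in the text reviewed, so trimming cannot be ruled out.

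The size may also be small. The ART example moves the RD by about 0.4 points even under strong heterogeneity, and the larger simulated gaps come from assumed selection and assumed effect modification. This stands too, although other covariates could add to the shift.

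Four stronger readings are tempting, and the SAP does not support them:

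- *The reported primary results are already mislabelled.* Nothing says that a fallback was used, and the balance tables point away from overlap weights.
- *The same rule governs the subgroups, where about 750 nifedipine users are divided further and overlap must be poor.* Part Three names no weighting or positivity rule, no subgroup overlap is reported, and smaller numbers alone do not create structural non-overlap.
- *The SAP treats stabilized and overlap weights as equivalent.* It lists them together as options and claims no equivalence.
- *The full-population ATE must be the only primary result.* The SAP makes positivity a condition for causal interpretation. If positivity fails, that ATE rests on extrapolation from the outcome model and not merely on a wide interval. Restricting the population, clearly labelled, is a legitimate answer.

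**Conclusion.** The point holds as a contingent labelling error. The SAP says that all estimators target the ATE, yet names two measures that do not. If overlap weights or trimming are used and effects vary between women, the result would be called an ATE and would describe the overlap population or the retained women. Stabilized weights are not affected.

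The change of population under overlap weighting can be illustrated (ART from about 9% to about 13%, or to about 5% with the opposite sign). The change in the RD or relative risk cannot be sized from the SAP, because it depends on unknown effect heterogeneity and, for trimming, on an unstated cut-off; it is nil if effects are constant on the scale reported. This is worth correcting because it is a stated rule and not just missing detail, and the correction costs almost nothing. It does not show that either primary result is wrong.

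**What to change.** Two edits to the SAP:

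1. In the Estimators text under Causal contrasts of interest, limit the statement that all estimators target the ATE to untrimmed IPW (including stabilized weights), regression adjustment, IPWRA and TMLE.
2. In section (A), add that any overlap-weighted or trimmed result is labelled with its own estimand (ATO, or ATE in the trimmed population), with the number excluded and the resulting population described, and is shown beside the untrimmed ATE estimate.

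If any result already produced used one of these measures, it should be relabelled in the same way.

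The cost is one additional reported estimate wherever a fallback is used. The untrimmed ATE shown there may be imprecise and may rest on model extrapolation, which the report should say.

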**(B) Outcome model using regression adjustment (RA)**

We will use a regression adjustment outcome model, incorporating appropriate variables as determined from directed acyclic graph (DAG) analysis.

**(C) Augmented inverse probability weighted regression adjustment model (IPWRA)**

This is one of the doubly robust methods which combines the IPW selection model with the RA outcome model. This provides two opportunities for correct model specification and may provide valid estimates if only one of the submodels is mis-specified.

**(D) Doubly robust targeted maximum likelihood estimation (TMLE), using machine learning algorithms**

TMLE model estimation uses the SuperLearner ensemble learning method. ^9,10^ This combines prediction to choose which algorithm within the library to use, based upon a weighting approach where weights are proportional to prediction performance for each algorithm assessed using cross-validation. TMLE uses data adaptive methods outlined in four steps^11^ and incorporates the pre-specification of a flexible suite of algorithms:

(i) Estimate model for expected outcome conditional on exposure and confounder set, and then use this model to predict the outcome for all records under exposure and non-exposure.

(ii) Estimate selection model for probability of exposure conditional on the confounder set.

(iii) Incorporate the PS information from step (ii) to improve the initial outcome prediction, so that they solve the parameter’s efficient influence curve – the smallest variance in the target parameter. The influence function is a function that describes the estimated behavior when the empirical distribution of the data is slightly perturbed.

(iv) Plus the updated prediction in the g-formulation (RA model) to estimate the ATE.

**Combining individual analysis model ATE into the population ATE estimator.**

Probability weighting induces within subject correlation in the outcome in the weighted sample resulting in biased (on the low side) standard errors (SE’s). While a robust SE setting in the analysis model does account for this lack of independence, it does not account for the fact that the propensity score is estimated, rather than known.

Alternatives include:

(i) Bootstrapping, where the propensity score is estimated within each bootstrap sample, and thus the bootstrap estimate of the standard error incorporates sampling variability in the estimated propensity score (BootImpute). ^12^

(ii) BootImpute von Hippel^13^, where the ATE variance estimate is calculated from an ANOVA model, and requires a smaller number of bootstrap samples and imputations.

We will integrate IPW with multiple imputation to calculate the pooled ATE. This will be performed using the BootMI von Hippel method. ^13^

In brief, we obtain B (B=1000) bootstrapped samples from the observational data; for each of the B bootstrapped samples, impute M datasets (M=2); the ATE point estimate is calculated as mean over all B times M complete datasets; a one-way ANOVA model is used to estimate the two variance components (within and between bootstrap samples), which are then used to estimate the standard error and construct associated 95% confidence intervals, incorporating Satterthwaite’s degrees of freedom correlation.

Consideration will be given to using Boot MI percentile, if computationally possible as a sensitivity analysis. In this procedure the first step is to obtain B (B=1000) bootstrapped samples from the observational data; for each of the B bootstrapped samples, impute M datasets (M=20 to 50); a point estimate is then calculated, and a 95% percentile-based confidence interval for the population parameter is generated by taking 2.5% and 97.5% empirical percentiles based upon the mean ATE of the M imputed datasets for each bootstrapped sample. ^12^

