**Details of imputation models**

|  | Observations per m | | | |
| --- | --- | --- | --- | --- |
| Variable | Complete | Incomplete | Imputed | Total |
| BMI | 7174 | 371 | 371 | 7545 |
| Smoking | 7471 | 74 | 74 | 7545 |
| SEIFA | 7542 | 3 | 3 | 7545 |
| IVF/ART Conception | 7521 | 24 | 24 | 7545 |
| Birthweight | 7532 | 13 | 13 | 7545 |

Observed raw data

| Variable | N | Mean | SD | Min | Max |
| --- | --- | --- | --- | --- | --- |
| BMI | 7174 | 31.71 | 7.50 | 10.01 | 59.88 |
| Smoking | 7471 | 0.16 | 0.37 | 0 | 1 |
| SEIFA | 7542 | 3.13 | 1.31 | 1 | 5 |
| IVF/ART Conception | 7521 | 0.09 | 0.28 | 0 | 1 |
| Birthweight | 7532 | 2926.36 | 734.23 | 160 | 5860 |

Imputed data bootstrap 1, m=1

| Variable | N | Mean | SD | Min | Max |
| --- | --- | --- | --- | --- | --- |
| BMI | 7545 | 31.69 | 7.49 | 10.01 | 59.88 |
| Smoking | 7545 | 0.16 | 0.37 | 0 | 1 |
| SEIFA | 7545 | 3.13 | 1.31 | 1 | 5 |
| IVF/ART Conception | 7545 | 0.09 | 0.28 | 0 | 1 |
| Birthweight | 7545 | 2922.03 | 741.39 | 160 | 5860 |

Imputed data bootstrap 2, m=2

| Variable | N | Mean | SD | Min | Max |
| --- | --- | --- | --- | --- | --- |
| BMI | 7545 | 31.69 | 7.51 | 10.01 | 59.88 |
| Smoking | 7545 | 0.17 | 0.37 | 0 | 1 |
| SEIFA | 7545 | 3.13 | 1.31 | 1 | 5 |
| IVF/ART Conception | 7545 | 0.09 | 0.28 | 0 | 1 |
| Birthweight | 7545 | 2922.11 | 741.21 | 160 | 5860 |

Proportions for SEIFA (m=1)

| **SEIFA Quintile** | **Observed** | **Imputed** | **Completed** |
| --- | --- | --- | --- |
| 1 | 0.154 | 0.333 | 0.154 |
| 2 | 0.163 | 0.333 | 0.163 |
| 3 | 0.266 | 0.000 | 0.265 |
| 4 | 0.237 | 0.000 | 0.237 |
| 5 | 0.180 | 0.333 | 0.180 |

Proportions for smoking status (m=1)

| **Smoking Status** | **Observed** | **Imputed** | **Completed** |
| --- | --- | --- | --- |
| Yes | 0.165 | 0.122 | 0.164 |
| No | 0.835 | 0.878 | 0.836 |

Proportions for IVF/ART conception (m=1)

| **IVF/ART Conception** | **Observed** | **Imputed** | **Completed** |
| --- | --- | --- | --- |
| Yes | 0.087 | 0.208 | 0.088 |
| No | 0.913 | 0.792 | 0.912 |

Proportions for BMI (m=1)

[figure not shown]

Proportions for birthweight (m=1)

[figure not shown]

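### The bootstrap interval recipe leaves out the robust standard errors meant to handle maternal clustering, does not name the mother as the resampling unit, and read literally pools the RR untransformed

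*SAP*

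**What the plan says.** Under *Causal contrasts of interest*, the SAP states: "We will use a logistic regression model with robust standard errors (to adjust for maternal clustering"). I found no other provision for clustering in the document. The same section defines the estimand as the ATE, "presented using both RD and RR metrics".

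The interval is built under *Combining individual analysis model ATE into the population ATE estimator*, in four steps:

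- Resampling: "we obtain B (B=1000) bootstrapped samples from the observational data".
- Imputation: two completed data sets are made from every resample.
- Point estimate: "the ATE point estimate is calculated as mean over all B times M complete datasets".
- Variance, with no reference to any standard error from the fitted model: "a one-way ANOVA model is used to estimate the two variance components (within and between bootstrap samples"). The standard error and a CI with Satterthwaite degrees of freedom follow from these components.

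An optional sensitivity interval is formed by "taking 2.5% and 97.5% empirical percentiles based upon the mean ATE of the M imputed datasets for each bootstrapped sample".

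Neither procedure names the unit that is resampled (infant, pregnancy or mother), and neither says whether the RR is averaged as RR or as log RR. The section does discuss robust standard errors, but for the correlation that weighting induces and for the estimated propensity score, not for births to the same mother.

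**The concern.** The two sections do not connect. A robust standard error corrects the variance that a single fitted model reports. The chosen method discards that variance and uses only how the point estimates vary between and within bootstrap samples. The clustering correction is therefore lost unless the resampling itself keeps each mother's births together. Multiple births are in the cohort, since plurality is a covariate, and twins share their mother's exposure. Ignoring that makes intervals too narrow, mainly for infant-level outcomes such as the neonatal primary composite.

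The second gap concerns the ratio. The sampling distribution of an RR is skewed to the right when events are few, and about 750 nifedipine women is a small arm. A plain mean with a symmetric interval then sets both limits too low. The error has a direction: under the null it yields too many intervals that seem to favour nifedipine and too few that seem to favour labetalol.

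**Working it through.** **1. What enters the variance.** Let θ(b,m) be the estimate from imputation m of bootstrap sample b. A one-way ANOVA gives the mean squares MSB and MSW. Then σ²(between) = (MSB − MSW)/M, and SE² = (1 + 1/B)·σ²(between) + MSW/(B·M), with B = 1000 and M = 2. Every term is a function of the θ(b,m). A robust standard error changes no θ(b,m), so it cannot change the SE. Only the resampling unit can bring clustering in.

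**2. Size of the clustering effect.** The SAP gives no multiple-birth rate, repeat-pregnancy share or ICC, so all three are assumptions. If all births of a mother share one exposure and k is her number of records:

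design effect = 1 + ICC × (Σk²/Σk − 1); record-level SE ÷ mother-level SE = 1/√(design effect).

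| Mothers with twins | Mothers with a repeat pregnancy | Σk²/Σk − 1 | Ratio, ICC 0.2 | Ratio, ICC 0.5 |
|---|---|---|---|---|
| 2% | 0% | 0.039 | 0.996 | 0.990 |
| 4% | 8% | 0.220 | 0.979 | 0.949 |
| 8% | 15% | 0.394 | 0.963 | 0.914 |

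Simulation of infants nested in mothers gave the same ratios to within 0.001 (0.996 down to 0.915). Coverage was about 92–95% by record and 94–95% by mother. In one complete run of the planned method on each of two invented data sets, the RD standard errors barely differed: 0.0172 by record and 0.0173 by mother (neonatal, 26% risk), and 0.0097 and 0.0094 (maternal, 5–6% risk).

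**3. Size of the scale effect.** *Anticipated sample size* gives about 7,500 women split 90/10, hence 6,750 and 750. At true RR 1 and risk p:

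s = SE(log RR) = √[(1 − p)/p × (1/6750 + 1/750)].

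The natural-scale interval is 1 ± 1.96·s; the log-scale interval is exp(±1.96·s). At p = 0.05, s = √(19 × 0.0014815) = 0.168. The last two columns give the chance that the interval falls wholly below / wholly above 1, summed over the two binomial distributions.

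| Assumed risk | Natural-scale CI | Log-scale CI | Natural misses | Log misses |
|---|---|---|---|---|
| 3% | 0.57–1.43 | 0.65–1.54 | 4.9% / 1.0% | 1.8% / 2.9% |
| 5% | 0.67–1.33 | 0.72–1.39 | 4.3% / 1.3% | 2.0% / 2.9% |
| 9.5% | 0.77–1.23 | 0.79–1.26 | 3.6% / 1.7% | 2.1% / 2.8% |
| 30% | 0.88–1.12 | 0.89–1.12 | 2.9% / 2.2% | 2.2% / 2.8% |

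Each side should miss 2.5%. The natural-scale limits are too low by 0.05–0.06 at 5% risk and by 0.08–0.11 at 3%, but by under 0.01 at 30%. In the invented maternal data set, with mothers resampled, the planned pooling gave RR 1.14 (0.80–1.47) on the natural scale and 1.12 (0.83–1.52) on the log scale.

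**4. Which risks are plausible here.** The SAP states no event rate. Its detectable differences (3.0% maternal, 5.6% neonatal) come without baseline rate, power or alpha, so they cannot be reproduced. Assuming two-sided alpha 0.05, 3.0% fits a labetalol rate of about 7.5% or 9.5% at 80% power, and about 5.0% or 7.5% at 90%. The two rates at each power depend on whether nifedipine is higher or lower. The 5.6% figure fits about 26% or 30% at 90% power; at 80% power the largest detectable difference at any baseline is about 5.4%. On these inferences the scale matters for the maternal primary and hardly at all for the neonatal primary.

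**The case against.** A reader might infer that the plan resamples records and pools the RR on its natural scale. It states neither. The bootstrap is given as a brief outline, and the analysts may well resample mothers. Predicted probabilities are said to yield both RD and RR, which leaves room to form the RR from pooled risks. This stands: both problems are conditional on how a silent text is carried out. It does not remove the point, because the one clustering provision the plan does state has no effect under the method it selects.

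The clustering effect is also small, and it rests on assumed inputs. Where a mother's drug differs between pregnancies, positive correlation would make record-level intervals too wide, so the direction is firm for twins but not for repeat pregnancies. This stands too.

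On scale, the RD has no such problem, the percentile interval is almost unaffected by it, and the individual components of both composites get summary statistics only. That confines the scale problem to the maternal primary and whichever secondary outcomes with a planned CI are uncommon.

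A further tempting inference is that resampling was never done. Under *Details of imputation models*, the tables labelled "Imputed data bootstrap 1, m=1" and bootstrap 2 have mean birthweights of 2922.03 g and 2922.11 g. Independent resamples would differ with an SD of about 12 g (734.23/√7545 = 8.45; × √2). But the imputed proportions match the original missing counts: 1/3 for SEIFA, 5/24 = 0.208 for ART and 9/74 = 0.122 for smoking. The tables look like ordinary imputation diagnostics on the unresampled file. They do not show that the 1,000 resamples were not drawn.

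**Conclusion.** The point holds as a defect in how the interval is specified. The robust standard errors do not enter the bootstrap variance, and the mother is not made the resampling unit. If records are resampled, standard errors are roughly 0–9% too small, mainly for infant-level outcomes. That range assumes 2–8% of mothers with twins, 0–15% with a repeat pregnancy, ICC 0.2–0.5, and one exposure per mother.

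Followed literally, the RR pooling gives limits that are too low for the less common outcomes: at 5% risk, misses of 4.3% and 1.3% instead of 2.5% a side. It is negligible near 30% risk and absent for the RD. The risks are inferred or assumed, not stated in the SAP.

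The documents do not support saying that clustering was in fact ignored, that published limits are wrong, or that resampling was skipped. At most, the bootstrap labels on the imputation tables should be checked. The change is worth making because it costs almost nothing and affects primary-outcome intervals.

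**What to change.** In *Combining individual analysis model ATE into the population ATE estimator*, state that:

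- mothers are resampled with replacement, each carrying all her pregnancies and infants;
- imputation and model fitting are repeated within each resample;
- the RD is pooled on its own scale, and the RR is pooled as log RR, with the estimate and limits then exponentiated;
- the optional percentile interval uses the same resampling unit.

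In *Causal contrasts of interest*, add that maternal clustering is handled by this resampling and not by the model's robust standard errors. Check the bootstrap labels on the tables under *Details of imputation models* and correct them if they describe the unresampled file.

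The cost is a cluster option in the bootstrap call and a log transform. Some intervals become slightly wider, and RR limits for uncommon outcomes move upward.
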